## Methods

### Design

This study protocol describes a two-arm parallel superiority RCT (allocation ratio 1:1). The trial has been designed to test the superiority of the experimental treatment (the UP) over the control condition (waiting list control group) in the improvement of depressive and anxiety symptoms, memory failures, dimensions of emotional disorders, emotional dysregulation, perceived stress, quality of life, distress tolerance and positive temperament in long COVID-19 participants.

The randomization sequence will be generated using the online platform randomizer.org to establish the order of group assignment (e.g., participant 1 = control; participant 2 = control; participant 3 = experimental; participant 4 = control; participant 5 = experimental; participant 6 = experimental…participant 90 = control). As participants enroll in the study, they will be assigned to the experimental or control group following this predefined sequence. Since the control group will remain on the waiting list for 12 weeks, participants cannot be blinded to their assignment condition. For the same reason, the researchers will also be aware of participants’ group assignments.

To ensure the transparency and methodological rigor of the study it was registered in clinicatrials.gov (registration identifier: NCT06928480; date of registration: May 22, 2025). Additionally, this study protocol adheres to the Standard Protocol Items: Recommendations for Interventional Trials (SPIRIT checklist [22]; see supporting information S1 Checklist).

### Trial status

Participant recruitment started on May 26, 2025 and is expected to conclude by December 31, 2026. Data will be collected during the recruitment period and will be finalized by the same date. Subsequent data analysis will be carried out once data collection is complete, with results expected to be available in 2027.

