After confirming the presence of at least one emotional disorder according to the Anxiety and Related Disorders Interview Schedule for DSM 5 (ADIS-5; [27]), participants will complete the online pre-treatment assessment protocol and will then be informed by email of their group assignment (either the experimental or the waiting list control group). Randomization to the experimental or group condition will be conducted by an independent researcher who will consult the pre-generated randomization sequence. The psychologist will also be informed of the assigned group to facilitate the management and organization of the UP-based experimental group intervention.

Participants in the experimental group will be required to complete an in-person additional assessment before they can begin the program. Accordingly, individuals assigned to the experimental group will meet in Zaragoza with a member of the research team to complete the neuropsychological and cognitive tests and to provide a hair sample for subsequent cortisol/cortisone analysis (secondary objective of this study). After these assessment point, participants will receive the UP-based psychological intervention in 12 online group sessions, each lasting 2 hours. Given that long COVID-19 patients often report cognitive difficulties [28] a break of approximately 10 minutes will be scheduled midway through each session. After the intervention, participants will complete the online post-treatment assessment protocol, which will include the measures administered at pre-treatment and a satisfaction questionnaire. Follow-up online assessments will also be conducted at three, six and twelve months after the intervention. At these time points, a group online session will be scheduled to monitor progress and reinforce the emotion regulation skills learned during the UP psychological program. At the three and twelve-month follow-up assessments, participants will repeat the in-person assessment to complete the neuropsychological and cognitive tests and to provide the hair samples for cortisol/cortisone analyses. Participants will receive email reminders for these appointments.

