In the case of participants who will be assigned to the waiting list control group, they will remain on the waiting list for 12 weeks and will not receive any psychological intervention. After this waiting period, they will complete the post-treatment assessment protocol and will then be enrolled in the experimental group following the same procedures previously described for this condition.

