#### Control group.

Individuals assigned to the control condition will remain on a waiting list for the 12 weeks it takes for the experimental group to receive the intervention. During this period of time, participants who are receiving follow-up for their physical health at any healthcare center may continue attending these appointments (i.e., regular visits with doctors, physicians, nurses, etc. to monitor the physical symptoms of long COVID-19). However, they will be asked not to initiate any additional psychological treatment until they have completed their participation in the study. For ethical reasons, once the post-treatment (t_2_) has been completed, participants in the control group will be offered the opportunity to join the experimental group.

Participants in both groups will be informed, both in the informed consent and also during the initial appointment with the research team, that they may withdraw from the study at any time. Likewise, the research team may recommend discontinuation if a worsening of symptoms is observed or if participants did not meet with the required procedures (i.e., attending to the sessions, responding questionnaires, providing hair samples, etc.)

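### The stated end of data collection coincides with the end of recruitment, which cannot be reconciled with a 12-week T2 and a 12-month follow-up

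*Protocol article*

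**What the plan says.** Trial status: "Participant recruitment started on May 26, 2025 and is expected to conclude by December 31, 2026". The next sentence reads "Data will be collected during the recruitment period and will be finalized by the same date", and the one after it "Subsequent data analysis will be carried out once data collection is complete, with results expected to be available in 2027".

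Procedures: "Follow-up online assessments will also be conducted at three, six and twelve months after the intervention". The face-to-face cognitive tests and hair sampling are repeated at two of these visits: "At the three and twelve-month follow-up assessments, participants will repeat the in-person assessment to complete the neuropsychological and cognitive tests". For controls, "they will remain on the waiting list for 12 weeks"; they then complete T2 and enter the intervention under the same procedures as the experimental arm. The Control group section confirms that the wait equals the 12 weeks of treatment.

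The Data analysis section models Time at five levels, T1 to T5. The aims in the Introduction include maintenance of benefit at 3, 6 and 12 months. The limitations paragraph of the Discussion says that comparison between groups is possible only at post-treatment and that only the experimental group will be available for follow-up.

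**The concern.** One calendar date serves both as the outer limit for recruitment and as the close of data collection. A person enrolled near that date has no time to complete 12 weeks of treatment or waiting, still less a further year of follow-up. No section sets an earlier last-enrolment date, shortens follow-up for late recruits or describes the missed visits as administrative censoring.

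If the dates are followed, two things suffer. T2 carries the whole randomised comparison, and some participants would have no T2 value for a reason unrelated to dropout, on top of the 20% dropout the sample size allows for. The 12-month maintenance, cognitive and cortisol/cortisone results would come only from people enrolled in the first months. If the schedule is followed instead, data collection runs into 2028, and a single analysis after its completion cannot give results in 2027. One of the statements has to change either way.

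**Working it through.** **Inputs**
- Recruitment from 26 May 2025 to 31 December 2026 at the latest; data collection closes on 31 December 2026 (Trial status).
- Treatment or waiting: 12 weeks = 84 days (Procedures; Control group).
- T3, T4 and T5 at 3, 6 and 12 months after the intervention (Procedures).
- 45 participants per arm, 90 in total; calculated sample size 74; dropout 20% (Participants).
- Assumed, because the article gives no figure: even accrual over the full window, and treatment starting on the day of enrolment.

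**Window.** 26 May 2025 to 31 December 2026 = 584 days.

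**Latest feasible enrolment** = closing date − follow-up interval − 84 days. For a crossed-over control, subtract a further 84 days. Share = days from 26 May 2025 to that date ÷ 584.

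| Visit | Latest enrolment | Days | Share of window |
|---|---|---|---|
| T2, either arm | 8 Oct 2026 | 500 | 85.6% |
| T3, UP arm | 8 Jul 2026 | 408 | 69.9% |
| T4, UP arm | 7 Apr 2026 | 316 | 54.1% |
| T5, UP arm | 8 Oct 2025 | 135 | 23.1% |
| T5, crossed-over control | 16 Jul 2025 | 51 | 8.7% |

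For crossed-over controls, 3 months gives (408 − 84)/584 = 55.5% and 6 months gives (316 − 84)/584 = 39.7%.

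**In participants, under even accrual**
- T2: 90 × 0.856 = about 77 of 90, so about 13 enrol too late. After 20% dropout, 77 × 0.8 = about 62 remain. Without truncation, 90 × 0.8 = 72. The calculated sample size is 74.
- T5, UP arm: 45 × 0.231 = about 10 of 45, before dropout.
- T5, crossed-over controls, if followed: 45 × 0.087 = about 4 of 45.

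**Sensitivity to a lag between enrolment and group start (assumed)**
- 4 weeks: T2 (500 − 28)/584 = 80.8%; T5 in the UP arm (135 − 28)/584 = 18.3%.
- 8 weeks: T2 (500 − 56)/584 = 76.0%; T5 in the UP arm (135 − 56)/584 = 13.5%.
- Even if the 12 months were counted from enrolment instead of from the end of treatment, only 219/584 = 37.5% could reach that visit.

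**The reverse calculation: recruitment to 31 December 2026 with the schedule kept**
- Last T2: 31 December 2026 + 84 days = 25 March 2027.
- Last T5, UP arm: 25 March 2028.
- Last T5, crossed-over control: 25 March 2027 + 84 days = 17 June 2027, plus 12 months = 17 June 2028.

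**The case against.** The strongest reply is that this is a slip in a status paragraph and not a design decision. The follow-up schedule is the same wherever it appears, only one sentence conflicts with it, and one date may simply have been given for two milestones. That is plausible, and it is why the point is classed as an inconsistency. It remains wrong as written, because someone following the stated date would stop collecting data too early.

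A second reply is that recruitment "is expected to conclude by December 31, 2026", which is an expectation and an outer limit, and that it may fill sooner because the target is fixed at 90. This stands in part. A reader might infer that most participants cannot reach 12 months, or that some will certainly miss T2. The document does not establish either, because both depend on when people enrol. The first is false if more than half of the UP arm enrolled in the first 135 of 584 days or if recruitment ends far earlier than stated. The second applies only to anyone enrolled after about 8 October 2026. Early completion eases the conflict more readily than it removes it: full T5 follow-up in the UP arm needs enrolment to end by about 8 October 2025, almost 15 months before the stated limit.

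Third, a reader might conclude that the maintenance objective fails altogether. That goes too far. Under even accrual 70% of the UP arm could still reach 3 months and 54% could reach 6 months. The mixed models use partial follow-up, and calendar truncation mainly costs precision. The weak point is 12 months.

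Fourth, the crossover figures depend on whether those participants' follow-up counts as trial data. Procedures implies that it does; the Discussion limitations imply that it does not. The UP-arm figures do not depend on the answer.

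**Conclusion.** The point holds as an internal inconsistency. The stated closing date and the stated schedule are incompatible if recruitment runs anywhere near its limit, and that follows from the calendar without any accrual assumption. So do the cut-offs of about 8 October 2026 for T2 and about 8 October 2025 for T5 in the UP arm.

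The shares (about 86% for T2; about 70%, 54% and 23% for 3, 6 and 12 months in the UP arm) rest on even accrual over the whole window and no start-up delay. Faster early accrual would raise them. Any lag lowers them, and they are lower for crossed-over controls if these are followed. On these assumptions the 12-month maintenance, cognitive and hormone analyses would rest on about 10 early UP recruits before dropout, and about 13 of 90 would have no T2 value for the between-group comparison.

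**What to change.** - Replace the single date with three: last enrolment, last T2 and last T5. With recruitment to 31 December 2026, T2 cannot close before late March 2027, nor T5 before late March 2028.
- Add an allowance for the in-person assessment before treatment and for forming groups. A lag of 4 to 8 weeks (assumed) would move the last UP-arm T2 to late April or late May 2027, and T5 by the same amount.
- Alternatively, keep the closing date and end enrolment correspondingly earlier.
- State whether crossed-over controls' follow-up is part of the trial data, so that Procedures and the Discussion limitations agree. If it is, T5 closes no earlier than mid-June 2028.
- Stage the reporting: the T2 comparison in 2027, and follow-up results after the last T5.

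The cost is a date amendment to the ethics committee, for which Procedures already provides a route, and a later follow-up report. The registry record was not available, so whether it also needs changing has to be checked. The T2 report can stay in 2027.

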### Participants

Participants will be adults residing in the Autonomous Community of Aragon (Spain) who have been diagnosed with long COVID-19 and meet criteria for at least one comorbid emotional disorder. Recruitment will take place at Hospital Royo Villanova from Zaragoza, Spain. An online dissemination campaign will also be conducted through social medial and in collaboration with the Long COVID-19 association from Aragón. Eligibility criteria to participate in the study are reported in Table 1. Participants will not be involved in the design, conduct or reporting the trial.

**Table 1 pone.0342908.t001:** Inclusion and exclusion criteria to participate in the randomized controlled trial.

Inclusion criteria	Exclusion criteria
Residing in the Autonomous Community of Aragon (Spain). Being at least 18 years old. Understanding of Spanish. Being diagnosed with long COVID-19: documented SARS-CoV-2 infection and persistence of symptoms beyond 12 weeks after the acute infection. Symptoms of depression (ODSIS≥7) and/or anxiety (OASIS≥8). Meeting the criteria for an emotional disorder diagnosis. Having access to the Internet. Signing the informed consent.	Pre-existing emotional symptoms prior to the acute SARS-CoV-2 infection. Currently receiving psychological treatment. Having a diagnosis of severe mental disorder (e.g., personality disorder, bipolar disorder, etc.). Active suicidal ideation at the time of the assessment. Individuals on psychotropic medication must maintain their dosage throughout the study, unless medically contraindicated.

Using the G*Power software [23], and taking into account the two study conditions, the five assessment points (pre-treatment, post-treatment, and follow-ups at 3, 6, and 12 months), as well as the statistical models planned for data analysis, we calculated a total sample size of 74 participants, achieving a statistical power of 90%, an alpha level of 0.05, and an effect size of 0.30. Considering an anticipated dropout rate of 20%, the required sample size is estimated at 45 participants per condition (total sample size = 90 participants).

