Despite the results of this study may have important clinical implications, we need to also acknowledge certain limitations. First, participants and researchers cannot be blinded to the intervention assignment, which may introduce expectancy effects. To minimize this potential bias, online assessments will be conducted so that the researchers are not involved in evaluating the efficacy of the intervention. Second, although sample size has been estimated to be sufficient to detect moderate effects, it may limit generalizability to broader populations or to patients with higher or lower long COVID-19 severities. Third, digital literacy of potential participants may interfere or even impede their participation in the study. For instance, participants may present difficulties to engage with the online platform to respond to the psychological assessments or they may find difficulties to engage in the online sessions through videocalls. These potential technology-related challenges will be partially mitigated by the support of the therapist who will explain the procedures for completing the assessment protocol and engaging in the online sessions. Additionally, satisfaction questions regarding the online format will also be included to capture participants’ opinion about the intervention and to evaluate whether these issues have been adequately addressed. Related with participants’ interest in this study, it is possible that some participants may show reluctance when asked to provide a hair sample. To minimize this potential concern, the research team will explain to participants that the hair sample consists of collecting only 5–6 strands from the back of the head and it will not affect their physical appearance. Finally, another potential limitation is that, for ethical reasons, participants in the control group will be offered the opportunity to join in the experimental group after completing the post-treatment assessment. Consequently, only the experimental group will be available for follow-up assessments, and comparisons between groups will be limited to the post-treatment time point.

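### The 90% power is justified with two arms at five assessments, but the arms can be compared only at post-treatment, where power is about 72% under the planned model (correlation 0.5)

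*Protocol article*

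**What the plan says.** The Participants section describes a G*Power calculation made by "taking into account the two study conditions, the five assessment points (pre-treatment, post-treatment, and follow-ups at 3, 6, and 12 months" and by the planned statistical models. It arrives at 74 participants, "achieving a statistical power of 90%, an alpha level of 0.05, and an effect size of 0.30". It then states: "Considering an anticipated dropout rate of 20%, the required sample size is estimated at 45 participants per condition (total sample size = 90 participants". It does not name the G*Power test, say which metric the 0.30 is in, or give a correlation between repeated measures.

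The Design section calls the trial a "two-arm parallel superiority RCT (allocation ratio 1:1").

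Under Procedures, controls wait 12 weeks. "After this waiting period, they will complete the post-treatment assessment protocol and will then be enrolled in the experimental group". The Discussion draws the consequence itself: "comparisons between groups will be limited to the post-treatment time point".

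The Data analysis section plans, for each outcome, a mixed model with Time (T1 to T5), Group, their interaction and a random intercept. The score at T1 is one of the outcome levels; there is no baseline covariate.

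**The concern.** The calculation counts five assessments in two arms. Randomised controls supply two, and only T2 can show a treatment difference, because randomisation makes the expected difference at T1 zero. Averaging five correlated measurements per person reduces the variance of an arm mean, so a calculation that assumes five waves in both arms reports more power than a comparison at one post-randomisation wave.

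Both primary outcomes, depressive symptoms (ODSIS) and anxiety symptoms (OASIS), are judged between arms at T2. If the 90% does not apply there, the chance of missing an effect of the planned size is larger than the 10% that the article implies, and a non-significant result would be weighed against the wrong figure.

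**Working it through.** **Inputs from the protocol article.** Alpha 0.05, power 90%, effect size 0.30, two groups at 1:1, five assessments, 74 evaluable, 90 enrolled, 20% dropout (Participants; Design). Controls are measured at T1 and T2 only (Procedures), and the arms are compared at T2 only (Discussion).

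**Assumptions, because the article does not give them.** The 0.30 is Cohen's f, so d = 2f = 0.60 for two equal groups. The correlation ρ is 0.5, with a range of 0.3 to 0.7. Tests are two-sided.

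**Step 1: reproduce the 74.** Take the repeated-measures ANOVA test for a between-subject factor, with m waves:

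λ = N·f²·m / [1 + (m − 1)ρ], on 1 and N − 2 degrees of freedom.

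With N = 74, f = 0.30, m = 5, ρ = 0.5: λ = 74 × 0.09 × 5 / 3 = 11.1, and power is 0.908. At N = 72 power is 0.8999, just short of 0.90. The smallest even N is therefore 74, the article's figure. This test assumes the same arm difference at every wave, including T1, where none is expected, and T3 to T5, where there is no control arm.

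**Step 2: power at T2 under the planned model.** With controls at T1 and T2 only, the between-arm effect in the Time × Group model is the difference in change from T1 to T2. A change score has SD √[2(1 − ρ)] in units of the outcome SD, so

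noncentrality = 0.60 / √[2(1 − ρ)] × √(N/4), on N − 2 degrees of freedom.

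At N = 74 and ρ = 0.5 this is 0.60 × √18.5 = 2.58, and power is 72.1%.

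**Step 3: power at T2 with baseline adjustment (not the planned model).** The residual SD is √(1 − ρ²), so

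noncentrality = 0.60 / √(1 − ρ²) × √(N/4), on N − 3 degrees of freedom.

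At N = 74 and ρ = 0.5 this is 2.98, and power is 83.6%.

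| Evaluable N | ρ | Difference in change (planned) | Baseline-adjusted |
|---|---|---|---|
| 74 | 0.3 | 57.6% | 76.1% |
| 74 | 0.5 | 72.1% | 83.6% |
| 74 | 0.7 | 90.8% | 94.6% |
| 72 | 0.5 | 70.9% | 82.6% |
| 90 | 0.5 | 80.4% | 90.1% |

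The 72 is what 90 enrolled leave after the stated dropout: 90 × 0.80 = 72.

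**Step 4: effect detectable with 90% power at ρ = 0.5.** For the difference in change, d = 0.76 at 74 evaluable and about 0.77 at 72. With baseline adjustment, d = 0.66 and 0.67.

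**The case against.** Four points can be made for the plan.

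- **The test is not stated.** This stands. The article names no test family, metric or correlation, and the match in Step 1 is not unique. A Time × Group interaction with f defined from partial eta-squared, λ = f²(N − 2)(m − 1)ε, also gives 74 with five waves and ε = 0.5, or with three waves and ε = 1; with five waves and ε = 1 it gives 46. A reader might infer that the sponsor is shown to have powered a group main effect, or a test foreign to the plan. The documents support neither: the first is an inference, and the Data analysis section lists the group main effect beside time and the interaction without ranking them. The point does not need the attribution, because the article itself says that it used five assessments in two conditions.
- **The correlation is unknown.** This also stands. At 74 evaluable, power reaches 90% at ρ of about 0.62 with baseline adjustment and about 0.69 for the difference in change. The result is therefore conditional, and the full range is 58% to 95%.
- **Dropout by T2 may be lower than 20%.** If all 90 were evaluable, power at ρ = 0.5 would be 80% for the planned contrast and 90% with baseline adjustment.
- **The limitation is disclosed.** The Discussion does say that the arms are compared only at post-treatment and claims no more than enough participants for moderate effects. It does not carry that limit back to the 90%, which stands uncorrected.

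**Conclusion.** The power justification is wrong as written: it relies on five assessments in two arms, while the design gives a between-arm comparison at T2 only. On the assumption that 0.30 is Cohen's f and applies at T2, the planned contrast with 74 evaluable participants has about 72% power at ρ = 0.5 (58% at 0.3, 91% at 0.7). A baseline-adjusted comparison would have about 84% (76% to 95%). At ρ = 0.5 the type II error is thus about 28% under the planned model, or 16% with adjustment, against the implied 10%.

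The contradiction itself needs no assumption; its size does. A reader might infer that the trial is certainly underpowered or must recruit more. The documents do not establish that: they give no correlation, and a high one would bring power to 90% with the numbers planned.

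**What to change.** Keep 90 participants. In the Participants section, remove the five assessment points from the justification, say that 0.30 is Cohen's f (if it is), state the assumed correlation, and restate power for the T2 contrast under the planned model. For example:

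> With 72 to 74 evaluable participants, the between-group difference in change from T1 to T2 has about 71–72% power for d = 0.60 at a correlation of 0.5, or 90% power for d of about 0.77.

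If the sponsor prefers to quote about 83–84% power (90% for d of about 0.66 to 0.67), the analysis of the T2 contrast must also change to adjust for the baseline score, and that change must be declared. The baseline score is already collected, so no new data are needed.

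The first option costs only rewording and a less favourable power figure. The second also costs a documented change to the analysis, best made before any outcome data are analysed.

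### The planned 90 participants, less the anticipated 20% dropout, leave 72 and not the 74 the protocol says it needs; power stays at about 90%

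*Protocol article*

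**What the plan says.** The sample size statement is in the Participants section of the protocol article, directly after the eligibility table. It takes account of "the two study conditions, the five assessment points (pre-treatment, post-treatment, and follow-ups at 3, 6, and 12 months", reports that "we calculated a total sample size of 74 participants", and gives the settings as "achieving a statistical power of 90%, an alpha level of 0.05, and an effect size of 0.30". The next sentence makes the allowance for losses: "Considering an anticipated dropout rate of 20%, the required sample size is estimated at 45 participants per condition (total sample size = 90 participants".

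The Design section describes a "two-arm parallel superiority RCT (allocation ratio 1:1" trial, so 74 means 37 per arm. The article does not print the formula that takes 74 to 90. It does not say that 74 already includes losses, and it gives no other dropout rate.

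**The concern.** The only purpose of the second sentence is to give a number to enrol such that, after the anticipated loss, the calculated requirement is still met. A reader can check it in one step, and it fails: 90 less 20% is below 74. The requirement, the dropout rate and the enrolment target cannot all be right together.

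What is at stake is the accuracy of a key design statement. The final report will be read against it, and if dropout turns out exactly as forecast, the trial will end with fewer participants than the protocol calls necessary.

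**Working it through.** **Inputs from the Participants and Design sections.** Requirement 74 (37 per arm), dropout 20%, enrolment 90 (45 per arm), allocation 1:1, power 90%, alpha 0.05, effect size 0.30, two groups, five measurements.

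**Inputs assumed, because the article does not state them.** The effect size is Cohen's f. The test is the between-groups F test of a repeated-measures ANOVA. The correlation between measurements is 0.5.

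**Step 1: reproduce 74.** The noncentrality is λ = f² × N × m / (1 + (m − 1)ρ), with 1 and N − 2 degrees of freedom. With f = 0.30, m = 5 and ρ = 0.5, λ = 0.09 × N × 5 / 3 = 0.15N. The smallest even N with power of at least 0.90 is 74, which matches the protocol. The result depends on the assumed correlation:

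| Correlation | Total N for 90% power |
|---|---|
| 0 | 26 |
| 0.3 | 54 |
| 0.5 | 74 |
| 0.7 | 92 |
| 0.8 | 102 |

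Of the values tried, only 0.5 returns the protocol's figure.

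**Step 2: reproduce 90.**
- Multiplying by 1 + d, per arm: 37 × 1.20 = 44.4, rounded up to 45, total 90. This matches.
- Multiplying by 1 + d, on the total: 74 × 1.20 = 88.8, rounded up to 89, or 90 when made even for two equal arms.
- Dividing by 1 − d, per arm: 37 / 0.80 = 46.25, rounded up to 47, total 94. This does not match.
- Dividing by 1 − d, on the total: 74 / 0.80 = 92.5, rounded up to 93. This does not match.

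**Step 3: apply the dropout to the stated target.**
- 90 × 0.80 = 72 (36 per arm); 74 − 72 = 2 short.
- Largest loss that still leaves 74 of 90: 1 − 74/90 = 16/90 = 17.8%.
- Smallest balanced total that protects 74: 92 × 0.80 = 73.6 is too few; 94 × 0.80 = 75.2 is enough. That is 4 more than 90.

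**Step 4: effect on power, under the Step 1 model.**

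| N | λ = 0.15N | Power |
|---|---|---|
| 72 | 10.8 | 0.900 (0.8999 unrounded) |
| 74 | 11.1 | 0.908 |
| 90 | 13.5 | 0.953 |

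As a check that does not use the assumed f and correlation, set λ so that the same F test has exactly 90% power at 74 (λ = 10.80). Scaling it by 72/74 gives 0.892 at 72. Either way the two missing participants cost about 0.8 percentage points.

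Steps 2 and 3 use only the protocol's own figures. Steps 1 and 4 depend on the assumptions above.

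**The case against.** The strongest reply is that nothing of substance changes. Under the model that yields 74, power at 72 is 0.8999, which is 90% at the precision the protocol uses. The figure of 74 already carries a small margin, because it is the first even total to pass 0.90. A dropout forecast is itself a rounded guess, and 17.8% against 20% is well inside its uncertainty. All of this stands, and it is why the point is minor.

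A second reply is that the article never calls the 74 completers. The Data analysis section plans linear mixed-effects models, which keep participants with incomplete data, and the Procedures section has everyone complete the pre-treatment assessment before learning their allocation. Counting every dropout as wholly lost is therefore the conservative reading. This stands in part. A participant with only a baseline value adds little to the group comparison, and the limitations in the Discussion restrict that comparison to post-treatment. More to the point, the protocol itself chose to inflate 74 for dropout, so its sentence should be true on those terms.

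Three stronger readings are tempting and not supported. A reader might infer that the trial is underpowered; the calculation above shows power essentially unchanged. A reader might infer that four more participants must be enrolled; a gap of under one percentage point does not call for that. A reader might take the multiplication by 1.20 as established; it fits the 45 per arm exactly, but the article does not show its formula.

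**Conclusion.** The point holds as an arithmetic inconsistency of minor severity. The shortfall is 2 participants after dropout, or 4 at enrolment under equal allocation. This follows from the stated 74, 20% and 90 and needs no outside assumption. The likely cause, an allowance multiplied by 1 + d when it should have been divided by 1 − d, is an inference from an exact match.

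The claim of 90% power is not overturned. On the assumptions that reproduce 74, it remains about 90% with 72 participants. If the sponsor's effect-size metric, test or correlation differed from those assumed here, the power quoted for 72 would need to come from the sponsor's own settings; the headcount would not change.

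**What to change.** Keep 90 and rewrite the dropout sentence in one of two ways:

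- State that, of 90 randomised (45 per condition), 72 are expected to remain if 20% drop out, and give the power for 72 from the same G*Power settings that produced 74 (about 0.90 under the assumptions used here).
- State that 90 randomised retains the required 74 provided dropout is no more than 17.8%.

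The cost is one sentence and a marginally less favourable figure. Enrolment, design and analysis stay as they are. According to the Trial status section, recruitment is expected to run until December 31, 2026 with analysis afterwards, so the correction can be made before any results are known.
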